### Data analyses

Descriptive statistics will be used to present group characteristics (e.g., sex, age, MMSE, medication use, comorbidities, side of fracture and the use of an assistive device), therapy adherence and adverse events. Baseline characteristics will be compared between groups with one-way ANOVAs. Given the explanatory objective of this study regarding the efficacy of C-Mill gait adaptability training, data will be analyzed per protocol, which implies that we will only include data of participants who completed at least 4 weeks of training and pre-intervention and post-intervention assessments (i.e., both T0 and T1). For longitudinal outcome measures (FAC, POMA, EMS, VAS, FES-I, TMT, NEADL, 10MWT, 10MWT_cognitive_, 10MWT_obstacle_, TUG, HOOS), multilevel regression analyses will be applied, which is appropriate for analyzing longitudinal data in which observations within one participant over time are correlated [61]. In addition, multilevel regression analyses account for missing values and allow baseline covariates to control for potential differences in baseline characteristics between groups [61].

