### Intervention program

The intervention programs will be dose-matched in terms of duration (i.e., 40 minutes per session) and frequency (i.e., five sessions per week) of therapy over a 6-week inpatient intervention period. All intervention programs will be provided by physical therapists of Solis Zorggroep, Deventer, The Netherlands. Therapy sessions will typically be conducted by a single physical therapist with two participants per session; the two participants alternately exercise and rest, resulting in 20 minutes of practice per session. Physical therapists and participants cannot be blinded to group allocation.

In the *usual care* (UC) control group, participants will receive conventional physical therapy in all 30 sessions, consisting of exercises of upper-leg strength, balance, transfers, overground walking, and activities of daily living, following locally implemented guidelines of Solis Zorggroep, Deventer, The Netherlands and Deventer Hospital, Deventer, The Netherlands regarding the treatment of hip fractures.

In the *conventional treadmill* (CT) intervention group, participants will receive 15 conventional physical therapy sessions (as in UC) and 15 conventional treadmill training sessions (week 1-3: 2 per week, week 4-6: 3 per week) with an emphasis on repetitive stepping. Participants will walk at comfortable treadmill walking speed, without body-weight support other than handrail support. Comfortable treadmill walking speed will be determined at the beginning of each session in order to promote the quality and safety of walking as appraised by the physical therapist. The initial focus of conventional treadmill training will be on the quality and safety aspects of walking: therefore, therapists may give instructions regarding the walking pattern. After a safe walking pattern has been established, the focus will gradually shift towards walking faster and longer. Participants in the CT group will walk on the C-Mill treadmill (C-Mill, ForceLink, Culemborg, The Netherlands), but without projection of visual context on the belt’s surface.

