
**Figure 3 F3:**
[figure not shown]
**Examples of C-Mill gait adaptability exercises.** Participants practice visually guided stepping to a sequence of regular or irregular stepping targets (**A**), obstacle avoidance (**B**), speeding up and slowing down by maintaining position in a moving walking zone (**C**), and all of the above in a functional and interactive gait adaptability game (**D**).

Note that we predict that the intensity of training, in terms of number of performed steps, will be markedly higher for both treadmill training intervention groups (i.e., AT and CT) than for the UC control group. We will test this prediction by comparing the number of steps taken per session among groups. To this end, the number of steps taken during AT and CT training sessions will be registered using the treadmill’s step counter while an observer will count the number of steps taken during UC sessions in a random sample of participants. We expect a main effect of Group in a one-way ANOVA, with post-hoc independent *t*-tests revealing significantly fewer steps for the UC control group than for both AT and CT training groups, in the absence of a significant difference between the latter groups.

To assist the therapist in progressively scaling the AT and CT training sessions, the participant’s perceived rate of fear and difficulty during AT and CT sessions will be assessed at a scale from 0 (no fear/not difficult) to 10 (much fear/very difficult), as well as their perceived rate of exertion using the 15 grade Borg scale (range 6-20, [37]).

Finally, adherence will be reported and the content of all individual training sessions will be registered by the supervising physical therapist. Adverse events during training sessions will be reported as well, and after completing the last UC, CT or AT therapy session of the intervention period, participants will fill out a purpose-designed questionnaire to register perceived discomforts during and after training sessions. The participant’s experience with the therapy program will be evaluated with this questionnaire as well to be able to compare the feasibility of the interventions from a participant’s perspective.

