### Sample size

We used the POMA [38] to perform a sample size calculation, because the POMA is a generic and widely used test to evaluate walking ability and has been associated with risk of falling [39,40]. Earlier clinical trials in which the POMA was used as an outcome measure reported mean differences of 4.0 and 3.5 POMA points between the intervention and control group [59,60]. The average standard deviations at follow-up measurements in these studies were respectively 3.8 and 4.8 POMA points. Assuming the lowest difference in mean value between groups (i.e., 3.5 POMA points), the highest standard deviation (i.e., 4.8 POMA points) and a correlation coefficient of 0.7, a sample size of 32 participants in each group is required to achieve 80% power with a two-tailed conservative alpha of 0.017 that is corrected for multiple comparisons. This sample size is based on the formula given by Twisk [61] to compare longitudinal outcome measures between groups.

We will include 126 participants who complete at least four weeks of intervention and pre- and post-intervention assessments (i.e., T0 and T1). Hence, participants who do not adhere to the protocol will be replaced to maintain a valid per-protocol assessment of sufficient power. In addition, this sample size allows for a maximum drop-out rate of 24% from T1 to T3.

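### The completer-only rule is worded for all data, so it is not clear that adverse events and adherence will be summarised for participants who stop early, miss T1 or are replaced

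*Protocol article*

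**What the plan says.** Four statements in the protocol article bear on this.

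- **Data analyses, opening sentence.** Descriptive statistics are planned for group characteristics and for "therapy adherence and adverse events". No population is named.
- **Data analyses, two sentences later.** The choice of analysis is introduced as follows: "Given the explanatory objective of this study regarding the efficacy of C-Mill gait adaptability training, data will be analyzed per protocol". The section then spells out the consequence for who is counted: "which implies that we will only include data of participants who completed at least 4 weeks of training and pre-intervention and post-intervention assessments". The only stated reason is the efficacy objective. The rule applies to data in general, with no exception for safety or adherence.
- **Sample size.** "We will include 126 participants who complete at least four weeks of intervention and pre- and post-intervention assessments", and "participants who do not adhere to the protocol will be replaced to maintain a valid per-protocol assessment of sufficient power".
- **Intervention program, text after Figure 3.** "adherence will be reported and the content of all individual training sessions will be registered by the supervising physical therapist", and "Adverse events during training sessions will be reported as well". Neither promise is confined to completers, and neither names a population.

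The article names no safety set and no all-randomised set.

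**The concern.** A per-protocol restriction can be argued for an explanatory efficacy comparison. That argument does not carry over to harms or adherence. An adverse event that ends training in the first weeks, or that prevents the T1 visit, is among the most informative events for safety, and it is the kind that a completer-only summary leaves out. Adherence described only among people kept because they stayed is selected on the quantity it is meant to describe.

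Treadmill walking soon after a hip fracture is the added exposure in two of the three arms. If it led to more early stopping than usual care, readers would need to see that by arm. The point concerns only the safety and adherence summaries. It would stand even if the per-protocol efficacy comparison were accepted.

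**Working it through.** **Step 1. Who has a place in the counts.** The target is 126 completers, so 126 / 3 = 42 per arm. The 24% allowance covers loss from T1 to T3 only: 42 × (1 − 0.24) = 31.9, which matches the 32 per group in the Sample size section. Loss before T1 is therefore met by replacement, not by the allowance. If a fraction q of those randomised fails the completer rule, 126 / (1 − q) must be randomised. The article gives no q. Assumed values:

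| q | Randomised | Outside the completer set |
|---|---|---|
| 5% | 126 / 0.95 = 132.6, so 133 | 7 |
| 10% | 126 / 0.90 = 140 | 14 |
| 15% | 126 / 0.85 = 148.2, so 149 | 23 |

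The article does not say where these people appear in the adverse-event and adherence summaries.

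**Step 2. Effect on the adverse-event proportion.** Let c be the proportion of completers with an event and f the proportion among those excluded. The proportion over everyone is c(1 − q) + fq. A completer-only table shows c, so it understates by q(f − c). The direction depends on f exceeding c, which is plausible when events cause stopping but is not shown in the article. Assume c = 10%:

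| q | f = 100% (every exclusion due to an event) | f = 50% | Completer-only table |
|---|---|---|---|
| 5% | 0.095 + 0.05 = 14.5% | 0.095 + 0.025 = 12% | 10% |
| 10% | 0.09 + 0.10 = 19% | 0.09 + 0.05 = 14% | 10% |
| 15% | 0.085 + 0.15 = 23.5% | 0.085 + 0.075 = 16% | 10% |

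**Step 3. Effect on a comparison between arms.** Take q = 15% in a treadmill arm and 5% in usual care, with f = 100% and c = 10% in both (assumed). The true difference is 23.5% − 14.5% = 9 percentage points. The completer-only table shows 10% − 10% = 0.

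**Step 4. Effect on adherence.** The programme is "five sessions per week) of therapy over a 6-week inpatient intervention period", so 5 × 6 = 30 sessions. Assume that completers attend 90% of sessions and excluded participants 33%. Mean adherence over everyone is 0.90(1 − q) + 0.33q:

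- q = 5%: 0.855 + 0.0165 = 87%
- q = 10%: 0.81 + 0.033 = 84%
- q = 15%: 0.765 + 0.0495 = 81%

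A completer-only summary shows 90% in each case.

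**Step 5. The two sections side by side.** Data analyses includes only completers' data. Intervention program promises adverse-event and adherence reports with no such condition and has the content of every individual session registered. An analyst could follow either one, and the resulting tables would differ.

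**The case against.** The strongest reply is that the rule was never meant for safety. The descriptive sentence comes first, without a restriction. The per-protocol sentence opens with the efficacy objective and leads into the multilevel models for the listed outcomes. The Intervention program section makes its own unrestricted promise to report adverse events and adherence. Replacement is justified by power and does not say that the records of replaced participants are discarded. Finally, defining a safety set is commonly left to an analysis plan, and none is shown.

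Much of this stands. The efficacy-only reading is possible, and a reader who infers that the plan deletes early-stop adverse events, or must report them as zero, goes further than the text. Nowhere does the article say that the safety summary is confined to completers.

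What does not stand is the conclusion that this is mere silence. The article states an exclusive rule about whose data will be included, in the paragraph that plans these summaries, and a later analysis plan would have to override it.

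A reader might also infer an attendance floor: four weeks schedule 4 × 5 = 20 of 30 sessions (67%), and in the treadmill arms 3 × 2 + 1 × 3 = 9 of 15 treadmill sessions (60%). The documents do not support such a floor. The rule sets weeks of training and no minimum attendance, so someone who missed sessions in those weeks could still qualify on this wording.

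**Conclusion.** The concern holds as a badly scoped rule. It does not show a settled intention to drop safety data. As worded, the completer restriction reaches the adverse-event and adherence summaries, its stated reason does not justify that, and it conflicts with the unrestricted promises in the Intervention program section. If it is followed literally, adverse events in participants who stopped before four weeks or missed T1 are left out, and adherence is described only in a group selected for staying.

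The size cannot be determined from the article. The range of 14.5% to 23.5% against 10% rests on three assumptions: 5% to 15% of participants stop early, every such stop is due to an adverse event, and 10% of completers have an event. If only half of those excluded had an event, the range would be 12% to 16%. The sample size is unaffected. The text should be corrected. Confidence is medium because the efficacy-only reading remains open.

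**What to change.** In Data analyses, attach the completer-only rule explicitly to the efficacy outcomes, and add wording such as:

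*Adverse events, reasons for stopping and therapy adherence will be summarised by arm for all randomised participants who started at least one session, including those who stopped before four weeks, missed T1 or were replaced. Adverse events will be given as participants affected and as events per session attended.*

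The per-session rate is useful because people who stop early have fewer sessions in which an event can be recorded. In Sample size, note that replacement concerns the efficacy set only and that replaced participants stay in these summaries.

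The cost is two or three sentences. The session records are already to be kept by the therapists, and neither the sample size nor any clinical rule changes. The downside is that the reported safety and adherence figures may look slightly less favourable.

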## Discussion

Falls are a common mishap among older adults and impose a major burden on older adults and the community at large; it is therefore important to gather evidence on the effectiveness of intervention programs and their design features (e.g., adaptive versus repetitive stepping, high versus low practice intensity). The current study was conceived to examine the efficacy of gait adaptability exercises in intervention programs aimed at improving walking ability and reducing fall incidence. Recently, encouraging first steps in this direction have been taken (e.g., [24,27,62,63]). Weerdesteyn et al. [24], for example, integrated overground gait adaptability exercises in a 5-week Nijmegen Falls Prevention Program for older adults, and found improved obstacle avoidance success rates, improved balance confidence and reduced fall incidence during one year follow-up. Given that the Nijmegen Falls Prevention Program consisted of overground walking, and hence practice intensity was presumably fairly low (i.e., number of steps taken per session), the observed beneficial effects are encouraging as they may be enhanced even further by increasing the practice intensity of gait adaptability exercises, such as with our C-Mill based gait adaptability training protocol.

In another encouraging study, Mirelman et al. [27] exploited the potential of virtual reality (VR) to practice step adjustments while walking on a treadmill. Participants’ feet positions were fed back in a virtual environment (i.e., a path with obstacles and targets) presented on a monitor in front of them. After 6 weeks of VR treadmill training, improved obstacle avoidance behavior, higher walking speed while performing a dual task and improved executive function (as assessed with the TMT) were observed for people with Parkinson’s disease. Also for people in the chronic phase after stroke, beneficial effects of VR treadmill training, using a head-mounted display [62] or a large screen in front of the treadmill [63], have been reported. All of these studies indicated that gait adaptability training with VR may help improve walking ability and reduce fall incidence in populations prone to falling. Note that C-Mill gait adaptability training is distinct from VR gait adaptability training in that C-Mill training elicits gait adjustments relative to visual context presented in the real environment, whereas with virtual reality training gait adjustments in the real world are detached from the context presented in the virtual environment. Given that gait adjustment is tied to task-relevant visual context in the VR environment only, VR gait adaptability training fails to utilize the direct visuomotor coupling of walking (e.g., [64-66]), where point of gaze is coupled to future foot placement locations, particularly in the presence of surface irregularities. Moreover, visuomotor control of targeted stepping deteriorates with aging, resulting in less accurate foot placement relative to stepping targets, especially in elderly with a high fall risk [67,68], but proved to ameliorate with training [69]. These examples illustrate the intimate relation between point of gaze and stepping accuracy relative to environmental context. The direct coupling between gaze and gait is fully exploited in C-Mill gait adaptability treadmill training in which step adjustments are elicited relative to visual context in the real environment (viz. augmented reality) rather than visual context in the virtual environment (viz. virtual reality). C-Mill gait adaptability training may thereby tentatively be even more effective than the abovementioned VR applications to practice step adjustments [27,62,63], which lack such a direct coupling.

The expected superior outcome of C-Mill gait adaptability treadmill training relative to conventional treadmill training is further supported by current insights into motor learning in the context of neurorehabilitation [70], which suggest that a considerable variability during practice enhances long-term training effects and transfer to new tasks and contexts compared to constant and repetitive practice (e.g., conventional treadmill training; [71-73]). Several theories of motor learning stress the importance of variability in training, including Schmidt’s schema theory [74], and theories of contextual interference [75] and differential learning [76]. These theoretical approaches have in common that one should exploit rather than eliminate variation in task performance to yield optimal learning effects in terms of retention and transfer. This insight is highly relevant for rehabilitation, which aims at long-lasting and general improvements. Exercises during C-Mill gait adaptability treadmill training, such as obstacle avoidance, visually guided stepping, speeding-up and slowing-down, and the interactive gait adaptability games, promote variable practice, which is further reinforced by varying obstacle size, moment of obstacle presentation, and the amount of variability in visually guided stepping (see Methods, Intervention program; see Additional file 1). This variable practice environment affords deep motor learning in that each step needs to be planned and executed from scratch in order to position it successfully relative to the visual context projected on the belt’s surface (e.g., [75]).

Gait adjustments to environmental context strongly rely on executive function [16,17], which comprises multiple cognitive processes including visual scanning, problem solving, planning, and task shifting (cf. the deeper form of motor learning referred to above). Interestingly, previous studies found indications for improved executive function after VR treadmill training with an emphasis on step adjustments [27], as measured with the Trail Making Test [43-45]. Such training induced changes in executive function are important because reduced executive function has been associated with gait impairments, reduced obstacle avoidance ability and falling [14,15,17]. Moreover, executive function is known to decline with age [17]. Considering that visual scanning, problem solving, planning, and task-shifting are integral elements in C-Mill gait adaptability treadmill training (i.e., to secure adequate foot placement relative to the projected environmental context), similar training induced improvements in executive function –which will be quantified by the Trail Making Test– may be observed in the present study for AT compared to CT and UC groups.

### Limitations

The inclusion and exclusion criteria for this study are deliberately quite broadly defined, such that the included patients are likely to be representative of the older population seen in daily clinical practice. This implies that the included patients likely exhibit various co-morbidities, resulting in heterogeneous study groups akin to the general population of older adults. On the one hand this may hamper between-group comparisons, but on the other hand findings may generalize well to mixed populations of older adults, which likely facilitates future implementation of the study’s results.

The use of vitamin D will not be intervened in the current study, implying that participants will not be supplemented with vitamin D as a standard. This resembles daily clinical practice, and may therefore also facilitate future implementation of the study’s results. However, since vitamin D supplementation has been associated with reduced fall rate and risk [5,7], supplementation will be reported in order to be able to control for vitamin D supplementation afterwards. Likewise, smoking history will be registered, since smoking is likely to adversely affect bone healing, bone mineral density, wound healing and the incidence of hip fractures [77-80].

Some outcome measures of walking ability (i.e., TUG, 10MWT, 10MWT_cognitive_ and 10MWT_obstacle_) will not be assessed at T0, mainly because pain and exertion will limit the number and content of conductible tests at T0. Comparing outcome measures not assessed at T0 between groups entails the risky assumption that groups do not differ at T0. To test this assumption, POMA, FAC and EMS, which are good indicators of walking ability, will be examined at T0. Results based on outcome measures not assessed at T0 should be interpreted with care. Other points of consideration include the different assessors at T0, T1, T2 and T3, and the different setting of T3, which is administered during a home visit. Although the performed tests are well standardized and have good validity and reliability [35,39,42-44,47,50,51,57], differences in test setting should be kept in mind when interpreting the results. The limitations in the current study mostly concern logistic choices based on clinical constraints, which are handled as well as possible to minimize bias.

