**Methods/design:**

The protocol describes a parallel group, single-blind, superiority randomized controlled trial with pre-tests, post-tests, retention-tests and follow-up. Hundred-twenty-six older adults with a recent fall-related hip fracture will be recruited from inpatient rehabilitation care and allocated to six weeks of C-Mill gait adaptability treadmill training (high-intensity, adaptive stepping), conventional treadmill training (high-intensity, repetitive stepping) or usual care physical therapy using block randomization, with allocation concealment by opaque sequentially numbered envelopes. Only data collectors are blind to group allocation. Study parameters related to walking ability will be assessed as primary outcome pre-training, post-training, after 4 weeks retention and 12 months follow-up. Secondary study parameters are measures related to fall incidence, fear of falling and general health.

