**Primary outcome measures related to walking ability**						
Performance Oriented Mobility Assessment (POMA)			x	x	x	x
10 Meter Walking Test with obstacles (10MWT_obstacle_)				x	x	
10 Meter Walking Test with cognitive task (10MWT_cognitive_)				x	x	
Trail Making Test (TMT)			x	x	x	x
Functional Ambulation Category (FAC)		x	x	x	x	x
Elderly Mobility Scale (EMS)			x	x	x	x
10 Meter Walking Test (10MWT)				x	x	
Timed Up-and-Go test (TUG)				x	x	
Nottingham Extended Activities of Daily Living (NEADL)			x		x	x

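### Four primary walking tests have no T0 value, and the plan answers with a weak test of baseline equality where it could commit to adjusting for T0 mobility scores it already collects

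*Protocol article*

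**What the plan says.** Table 1 of the protocol article places TUG, 10MWT, 10MWT_obstacle and 10MWT_cognitive under "Primary outcome measures related to walking ability", with marks at T1 and T2 only. The Limitations section confirms this: "Some outcome measures of walking ability (i.e., TUG, 10MWT, 10MWT_cognitive_ and 10MWT_obstacle_) will not be assessed at T0", giving pain and exertion as the main reason. It then says: "Comparing outcome measures not assessed at T0 between groups entails the risky assumption that groups do not differ at T0". The response follows directly: "To test this assumption, POMA, FAC and EMS, which are good indicators of walking ability, will be examined at T0". It closes with a caution: "Results based on outcome measures not assessed at T0 should be interpreted with care".

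The Data analyses section names one method for baseline comparison: "Baseline characteristics will be compared between groups with one-way ANOVAs". It lists the four tests among the outcomes for multilevel regression and notes that such models "allow baseline covariates to control for potential differences in baseline characteristics between groups". It names no covariate for any outcome. The same section restricts the analysis to participants with at least four weeks of training and both T0 and T1. The Sample size section says that non-adherers will be replaced.

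**The concern.** The protocol sets out a method for dealing with the missing T0 values, and the method does not do what is asked of it. A significance test cannot establish that arms are comparable. If it is non-significant, a difference large enough to matter may have gone undetected. If it is significant under intact randomisation, it has found a chance difference. Neither result changes the treatment estimate.

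The protocol itself regards POMA, FAC and EMS as good indicators of walking ability. Variables of that kind are useful as covariates, yet for these four tests they are named only as a check.

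The obstacle and cognitive walks matter most here. They come closest to the hypothesis that adaptability training is superior on the adaptability aspects of walking. A wider standard error than necessary falls on the comparison of most interest. Any baseline difference created by the per-protocol selection would also go uncorrected there.

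**Working it through.** **1. The plan's own figure.** Inputs from Sample size: difference 3.5 POMA points, SD 4.8, correlation 0.7, two-sided alpha 0.017, power 80%. The longitudinal two-group formula is

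n = 2(z_α + z_β)² · SD² · [1 + (T − 1)ρ] / (T · δ²).

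With z_α = 2.387 and z_β = 0.842, the part without the bracket and T is 2 × 3.228² × 4.8² / 3.5² = 39.2. The number of follow-up measurements T is not stated. T = 3 gives 39.2 × 2.4 / 3 = 31.4, so 32 per group, which matches. Allowing for 24% dropout, 42 × 0.76 = 31.9, so 126 in total also reproduces. This calculation rests on POMA, which has a T0 value, so the present point does not affect it.

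**2. How informative is the baseline test?** The assumed method is one-way ANOVA (the only one named for baseline), alpha 0.05, 42 per arm. With one arm shifted by d SD, the noncentrality is λ = 42 × 2d²/3, on 2 and 123 degrees of freedom (critical F = 3.07).

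| Shift d | λ | Power |
|---|---|---|
| 0.2 | 1.12 | 14% |
| 0.3 | 2.52 | 27% |
| 0.4 | 4.48 | 45% |
| 0.5 | 7.00 | 64% |

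If the three means are evenly spaced with extremes d apart, λ = 42 × d²/2 and power is lower: 21% at 0.3 and 51% at 0.5. If the arms are truly equal, three tests give at least one false alarm in up to 1 − 0.95³ = 14% of trials (independence assumed; fewer if the scores are correlated).

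**3. What adjustment gains under intact randomisation.** The residual variance at one visit is multiplied by 1 − R², where R is the multiple correlation of the T0 scores with the later time. The documents do not give R; the 0.7 in Sample size belongs to the POMA calculation. The range below is an assumption.

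| R | 1 − R² | SE factor √(1 − R²) | Effective n, 1/(1 − R²) |
|---|---|---|---|
| 0.3 | 0.91 | 0.95 (−5%) | 1.10 (+10%) |
| 0.5 | 0.75 | 0.87 (−13%) | 1.33 (+33%) |
| 0.7 | 0.51 | 0.71 (−29%) | 1.96 (+96%) |

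**4. What adjustment leaves behind.** POMA, EMS and FAC stand in for the unmeasured T0 time. If their correlation with that value is r, the share of chance-imbalance variance left after adjustment is 1 − r²: 75% at r = 0.5, 51% at 0.7 and 19% at 0.9.

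**5. Simulation (8,000 runs, two arms of up to 42, no treatment effect).** Assumptions: three proxies, each correlated 0.75 with the unmeasured T0 value; outcome correlation with that value 0.5 or 0.7.
- Intact randomisation: the unadjusted mean difference was 0.00 SD, so unbiased. Adjustment multiplied the SE by 0.91 and 0.80.
- Retention depending on the T0 value in one arm only: unadjusted bias was 0.13 and 0.18 SD, and adjusted bias was 0.03 and 0.04 SD. About a fifth remained.

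**The case against.** The strongest reply is that a randomised comparison of T1 and T2 values needs no baseline value. The unadjusted estimate is unbiased and its standard error already covers chance imbalance. That is right, and it limits the point: under intact randomisation precision is at stake, not validity. The power figures in step 2 also presuppose a real shift between the analysed groups, which randomisation alone does not produce. Selection into a per-protocol set with replacement could produce one, but the documents do not show that it will.

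A second reply is that the Data analyses section already provides for baseline covariates, and that a covariate list is commonly left to a SAP. This stands in part. An unnamed list would not be a finding. The point is that the protocol does state a specific response for these four tests, and that response is a test of equality.

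Third, the authors disclose the limitation and ask for caution. That is to their credit, but caution recovers no precision.

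A reader might infer more than the documents support:
- **That adjustment removes the problem.** It does not: the scores are proxies and cannot supply change from baseline.
- **That covariates will be chosen from the ANOVA results.** No passage says so.
- **That ANOVA will be applied to sex, fracture side or assistive device.** These are examples in the sentence on descriptive statistics; the ANOVA sentence lists no variables.
- **That the abstract is false in describing walking ability as** "assessed as primary outcome pre-training, post-training, after 4 weeks retention and 12 months follow-up". It speaks of walking-ability parameters collectively, several are measured at all four times, and Table 1 gives the exact schedule.

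**Conclusion.** The point holds as a recommended improvement to the analysis, not as a flaw that invalidates the comparison. For four tests listed as primary, the stated safeguard is a baseline test with roughly 27% power against a 0.3 SD shift in one arm, and its result says little about comparability either way. Using the same T0 scores as covariates would cut the SE by about 5% to 29%. That size depends entirely on an assumed multiple correlation of 0.3 to 0.7; the direction is secure if the T0 scores predict the later times appreciably, as the protocol's own description of them implies. Protection against selection in the per-protocol set is a further, partial benefit, and its size rests on the simulation's assumptions.

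**What to change.** In Data analyses and Limitations, replace the test of baseline equality with a commitment that the models for TUG, 10MWT, 10MWT_obstacle and 10MWT_cognitive include T0 POMA and T0 EMS as covariates, whatever imbalance is observed. Add T0 FAC if its range is not too narrow; entry requires a score of 2 or higher, so it may add little. That choice should be made on the pooled distribution, before outcomes are compared by arm. Present baseline data by arm descriptively, without significance tests. Keep the caution in Limitations, reworded to say that adjustment uses proxies and therefore reduces, but does not eliminate, dependence on T0 comparability in the per-protocol set.

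The cost is a change of wording and a few degrees of freedom. No new data are needed.
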